### Study design and data collection

This study is a correlational implementation study performed alongside a two-armed RCT [21]. The combined study can be described as a hybrid effectiveness-implementation type 2 trial [43, 44], although the implementation strategies are not tested per se. To test the four research hypotheses, we will include a quantitative longitudinal web-based data collection spanning three time points, among SPARCK practitioners and their leaders. The first time point (T1) was during the initiation of the intervention in 2023, shortly after training of practitioners and information dissemination to leaders. The second data collection (T2) was after approximately 1 year when the practitioners had completed two cases each. The last data collection (T3) will be conducted after approximately 2 years (2025), when the practitioners have completed four cases each. In addition, for hypotheses H2 and H3 concerning relations with clinical outcomes, we will also include parent reported data on child symptoms and parent–child interaction from the RCT at pre, post (treatment termination), and follow-up (6 months after post) [21].

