More specifically, in H1, which concerns implementation determinants as predictors of implementation outcomes, we will regress implementation outcomes at T2 on implementation determinants at T1. In essence, this means a potential two-level model (practitioners/leaders are nested within municipalities). To investigate H2, concerning a relation between implementation determinants and parent reported clinical outcomes, estimates of change from pre to post or pre to follow-up [21] in child symptoms will be regressed upon either a mean-variable of practitioner/leader reported implementation determinants at T1, T2, and T3, or practitioner/leader reported implementation outcomes as a time-varying covariate (predictor). The same strategy will be used to investigate H3, only with implementation outcomes as predictor. In these analyses, there are potentially three levels (families nested within practitioner/leader which are nested in municipalities). Importantly though, we aim towards a parsimonious model in which complexity in the model is introduced only if the first steps in the model suggest it is necessary (e.g., through high ICC and design effects). To investigate H4, concerning a positive development in ratings of implementation determinants and outcomes over time, a multilevel growth curve model with three levels (repeated measures [level 1], nested within practitioners/leaders [level 2], nested within municipalities [level 3]) could be a solution given the nesting in our data. However, as we have a small sample size and data over time is gathered with one year in between, we will consider a less complex model [52]. Across all analyses, model building will be conducted in a stepwise fashion and improvement will be assessed for each step [53, 54] through model comparisons using -2LL, AIC, and BIC. Thus, maximum likelihood estimation is used for model comparisons and restricted maximum likelihood for final parameter estimates. Missing data will be handled using full information maximum likelihood, in which all available data in the model contribute to the parameters in the final model [55]. Although we have not specified specific mediator and moderator analyses in the present protocol study, we will explore potential theoretically and empirically relevant mediators and moderators in cross-level mediation and interactions models. Finally, we will explore differences between municipalities involved in the optimization process and those not involved, to assess whether co-creation is associated with implementation outcomes.

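### H2 and H3: if the change outcome is one observed difference per family, the stated full information maximum likelihood does not retain families who miss the later assessment

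*Protocol article*

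**What the plan says.** Under Data analysis, the outcome for H2 is given as "estimates of change from pre to post or pre to follow-up" in child symptoms, regressed on staff-reported ratings. For H3, "The same strategy will be used to investigate H3, only with implementation outcomes as predictor". The potential levels for both are families, practitioners or leaders, and municipalities. A level for repeated measures is named only for H4, where the repeated responses come from staff.

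The predictor may be a mean over T1 to T3 or, alternatively, "practitioner/leader reported implementation outcomes as a time-varying covariate (predictor").

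The missing-data rule applies to all analyses: full information maximum likelihood, under which "all available data in the model contribute to the parameters in the final model".

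Study design and data collection says that the parent reports come "from the RCT at pre, post (treatment termination), and follow-up (6 months after post"), so up to three scores per family exist. The article gives no family drop-out rate and no planned number of families for H2 and H3.

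**The concern.** Full information maximum likelihood can use a partly observed family only through variables that the likelihood contains. With a single change value as the outcome, a family with a pre score and no later score has no outcome. Unless the pre score enters in some other way, that family is lost and the method gives no more protection than deleting it.

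The predictors rate how well SPARCK is received and delivered, which could plausibly influence which families stay. If more severe families leave mainly where ratings are poor, the families that remain there are milder and have less room to improve. Better ratings would then appear to go with more improvement, as H2 and H3 predict, without any true link.

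**Working it through.** The article states no figure to reproduce, so the check is an argument about the likelihood followed by scenarios. Drop-out here means a missing later parent report.

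**1. Who contributes.** Let y0 be the pre score, y1 the later score, x the staff rating and D = y1 - y0.
- Outcome D: each family contributes f(D | x). If y1 is missing, D is missing and the family's factor is 1. The likelihood is the same with or without that family.
- Outcomes y0 and y1 together: each family contributes f(y0 | x) f(y1 | y0, x). A family with only y0 still contributes f(y0 | x).

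**2. When the slope is biased.** Assume E[y1 | y0, x] = a + r y0 + b x, y0 unrelated to x among all families, and drop-out depending only on y0 and x. The target slope is b. Among completers,

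E[D | x, stay] = a + b x - (1 - r) E[y0 | x, stay],

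so bias = -(1 - r) d, where d is the slope of pre score on rating among completers. If drop-out depends on neither variable, or on only one of them, d = 0. It is also 0 if the chance of staying is a function of y0 times a function of x. Joint dependence is therefore necessary but not always sufficient. Large-sample checks at 27% drop-out gave a slope of 0.00 both for dependence on the pre score alone and for multiplicative retention.

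**3. Scenarios with no true link (b = 0).** From the article: 44 practitioners (Setting, participants, and recruitment) and four cases each by T3 (Study design and data collection), so 44 x 4 = 176 families. This number is derived, not stated. Assumed: pre-post correlation 0.5, severe families leaving more often where ratings are poor, 4000 runs per setting.

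| Drop-out | Interaction of pre score and rating | Completer slope (SD per SD) | Implied d = slope / -0.5 |
|---|---|---|---|
| 14% | no | -0.014 | 0.03 |
| 24% | no | -0.018 | 0.04 |
| 26% | no | -0.041 | 0.08 |
| 29% | no | -0.063 | 0.13 |
| 26% | yes | -0.074 | 0.15 |
| 30% | yes | -0.080 | 0.16 |

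The empirical SD of the slope was 0.09 to 0.10 and the false-positive rate 5.2% to 12.5%. As a check on the top value, -0.08 / 0.10 = -0.8, and Φ(-1.96 + 0.8) + Φ(-1.96 - 0.8) = 0.123 + 0.003 = 12.6%. The likelihood that keeps the pre scores had bias 0.00 in every setting. Repeat simulations agreed, with false-positive rates of 4% to 12% and no loss of precision for the joint likelihood.

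**4. Scenarios with a true slope of -0.30.** Here the log-odds of drop-out moved by 1 per SD of pre score and of rating (no interaction), or by 0.5 per SD with an interaction of 1.

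| Drop-out | Families kept | Unrelated to both | No interaction | With interaction | Joint likelihood |
|---|---|---|---|---|---|
| 10% | 158 | -0.30 | -0.33 | -0.36 | -0.30 |
| 20% | 141 | -0.30 | -0.35 | -0.39 | -0.30 |
| 30% | 123 | -0.30 | -0.36 | -0.42 | -0.30 |

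The worst case exaggerates the slope by 0.42 / 0.30 - 1 = 40%. The bias formula does not contain b, so the larger absolute values here (0.03 to 0.12) reflect a different assumed drop-out pattern. The pattern matters as much as the rate.

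**5. Direction.** If the pattern is reversed, so is the sign: +0.02 at 25% drop-out with moderate dependence, and +0.06 at 29% when milder families leave with strong dependence.

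**The case against.** A reader might infer that H2 and H3 certainly use a raw change score, that their slopes describe completers only, and that the results will lean towards the hypotheses. The article does not support that.

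- It speaks of estimates of change and cites the RCT protocol, which is not shown. A latent-change or growth model of the three scores would keep these families. The time-varying predictor also sits badly with a single value per family and hints at repeated outcomes.
- It lists no covariates. If the pre score is one, this bias mechanism is removed, although families without the later score still go unused.
- The missing-data sentence is limited to data in the model, so it is not false as written.
- A family missing only follow-up still counts in the pre-to-post analysis.
- No drop-out rate or pattern is given. In the scenarios without a true link the bias stays below the slope's own SD, and its direction follows from the assumed pattern.
- The 0.00 for the joint likelihood holds because drop-out was generated from the pre score and rating alone. If leaving depends on the unseen later score, neither model is safe.

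All of this stands, and it makes the point conditional. It does not remove it. The listed levels, set against those for H4, make one value per family the most direct reading, and on that reading the outcome and the missing-data method do not work together as a reader would expect.

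**Conclusion.** The point holds conditionally. If the change is an observed difference and the pre score is not otherwise in the model, the planned method is a complete-case analysis for family drop-out in each interval. Where drop-out does not depend jointly on pre score and staff rating, the cost is lost families and precision, not bias (taking pre score and rating as unrelated among all families). Where it does, the bias with no true link was negligible at about 14% drop-out and about 0.02 to 0.08 SD per SD at 24-30%, with a false-positive rate up to about 12%. Under the strong dependence of the second set it reached 0.03 to 0.06 already at 10%. These are scenarios resting on 176 derived families, a pre-post correlation of 0.5 and assumed drop-out patterns; they are not predictions. A bias in favour of H2 and H3 follows only if more severe families leave where ratings are poor. The point merits a change to the analysis wording.

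**What to change.** For H2 and H3, make the parent-reported pre, post and follow-up scores the outcome, one row per assessment, with assessments within families within practitioners and municipality added if the intraclass correlation calls for it. Test staff rating x time. Families with only a pre score then stay in the likelihood, and the time-varying predictor has repeated outcomes to act on. If a latent-change model was already intended, say so and state that the pre score is part of the likelihood.

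Also report the share of families without a post score and without a follow-up score by level of the staff rating, with a multilevel logistic model of drop-out on the rating.

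The cost is one more model level and slightly more analysis work. No extra data are needed. The article describes T3 as still to come, so the wording can be settled before the H2 and H3 analyses that use T3 ratings.

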
## Discussion

This protocol outlines the rationale and design of an implementation study of SPARCK into multiple sites in Norwegian municipalities. SPARCK is a carefully co-created and optimized parent training intervention for prevention of child mental health problems. In addition to evaluating the clinical effect of SPARCK in an RCT, we aim to investigate the importance of various implementation factors, as effectiveness and implementation research are stronger when conducted in tandem [14]. A dual focus on effectiveness and implementation represents a potential to speed up the uptake of an intervention, more effective implementation strategies, and more useful information for both researchers and decision-makers [43, 44].

How to improve effectiveness of interventions targeting child mental health problems, and how to optimize their implementation and sustained use constitute major challenges, both applied and scientific, within prevention and implementation research. If children and families do not have access to EBIs they could have profited from, the implications may be severe at both personal and societal levels and include prolonged suffering for the families. The presented study may generate much-needed knowledge on how implementation determinants impact clinical outcomes, as well as specific implementation outcomes. An additional aim of the study is to explore and report on implementation strategies that are needed to promote sustainable long-term outcomes of parent training interventions for prevention of child mental health problems in Norway and beyond.

Scientifically, the effectiveness study in this project may contribute to narrowing the knowledge gap on the effect of parent training interventions for child internalizing and externalizing symptoms [21]. The implementation study may contribute to the implementation science field with knowledge on how contextual barriers can affect both clinical effectiveness and specific implementation outcomes that are important in the initial phase of implementation. This knowledge is essential when choosing, tailoring, and deploying implementation strategies [6, 25, 26] to address barriers, and ultimately to promote success and sustainment when implementing EBIs beyond the scope of a research study and into the real world [18].

## Data Availability

A comprehensive plan outlining the procedures for the collection, handling, and storage of data has received approval from SIKT. To ensure the security and privacy of sensitive information, we use the University of Oslo’s Services for Sensitive Data (TSD) [58] for all data storage and analysis. We use Nettskjema [59], developed and operated by the University Information Technology Center, a TSD-integrated survey solution for collecting sensitive data. All study information, including participant identification keys and raw data, will be securely stored at TSD. Access to this information will be restricted to authorized personnel. We will implement measures to protect data confidentiality and integrity, including encryption of all data transfers and regular backups to safeguard against data loss. In the event of any breaches or unauthorized access, we will follow established protocols for reporting and responding to such incidents. The datasets generated in the current project are not publicly available due to the General Data Protection Regulation (GDPR) and Norwegian regulations but can be made available upon request.

## Abbreviations

AIM: Acceptability of Intervention Measure
CFIR: Consolidated Framework for Implementation Research
EBIs: Evidence-based interventions
ERIC: Expert Recommendations for Implementing Change compilation
FidQ: Fidelity Questionnaire
FIM: Feasibility of Intervention Measure
GDPR: General Data Protection Regulation
IAM: Intervention Appropriateness Measure
IDEAS: Innovate, Develop, Evaluate, Adapt, Scale Impact Framework
IDM: Implementation Determinant Measure
IRLM: Implementation Research Logic Model
MOST: Multiphase Optimization Strategy
NUBU: Norwegian Center for Child Behavioral Development
ORIC: Organizational Readiness for Implementing Change
PI: Principal investigator
PMTO: Parent Management Training—Oregon model
REK: Regional Committee for Medical Research Ethics in Norway
RCT: Randomized controlled trial
SCED: Single case experimental designs
SIKT: Norwegian Agency for Shared Services in Education and Research
SPARCK: Supportive Parents—Coping Kids
T1: Time 1
T2: Time 2
T3: Time 3
TIDieR: Template for Intervention Description and Replication checklist and guide statement
TSD: University of Oslo’s Services for Sensitive Data
UCD: User-centered design
